## Abstract

**Background:**

Osteoarthritis is a leading cause of disability in developed nations. In Australia it afflicts 16.5% of the adult population. Total joint arthroplasty is considered the treatment of choice for end stage osteoarthritis. The number of total joint arthroplasties undertaken in Australia has doubled over the last decade (more than 80,000 procedures in 2011). The incidence of pre-operative psychological distress in this group of patients is reported between 30% and 60% and pre-operative psychological distress is associated with poorer pain and functional outcomes after surgery. This study will use a mindfulness-based psychological intervention to enhance outcomes in people undergoing total joint arthroplasty and, in addition, will test hypotheses about coping with chronic illness in an aged population. This study is the first of its kind and will provide a greater understanding of the role of a mental health enhancement program on the physical recovery of total joint arthroplasty patients.

**Methods/Design:**

One hundred and fifty people with end-stage arthritis on the waiting list for total hip or knee arthroplasty will be recruited and randomly allocated to one of two groups using computer-generated block randomisation. A randomised controlled trial adhering to CONSORT guidelines will evaluate the efficacy of a mindfulness training program (weekly group-based classes in mindfulness practice, 2 ½ hours, for 8 weeks plus a 7-hour Saturday session in Week 6) prior to total joint arthroplasty, compared to a “standard care” group who will undergo routine total joint arthroplasty. Primary outcomes will be evaluated by a blinded examiner at baseline, 3 and 12 months post-surgery, using a validated self-reported pain and physical function scale. Secondary outcomes will include i) a range of validated measures of psychological wellbeing and ii) health economic analysis. All analyses will be conducted on an intention to treat basis using linear regression models. Health economic modelling will be applied to estimate the potential cost-effectiveness of mindfulness training and total joint arthroplasty.

**Trial registration:**

Australian New Zealand Clinical Trials Registry (ANZCTRN12611001184965). Date of registration; 15th November 2011.

## Background

Osteoarthritis is a leading cause of disability in developed nations. In Australia, it afflicts 16.5% of the adult population and imposes a significant economic burden [1]. Total joint arthroplasty (TJA) is considered the treatment of choice for end-stage osteoarthritis. However, the success of TJA, a high volume, expensive procedure, is undermined by pre-operative psychological distress, a known predictor of suboptimal improvement after surgery. Psychological co-morbidities and traits reported in TJA patients include depression, anxiety, neuroticism, catastrophizing, poor self-esteem, and low self-efficacy, all of which are associated with poorer function and greater pain after TJA in short and longer term follow-up studies [2-7].

Our recent comprehensive literature review found pre-operative psychological distress to be an independent predictor of pain and function after TJA in a majority of published studies [8]. This relationship has also been noted for other major surgical procedures, e.g., herniated disc surgery [9] and coronary artery bypass graft surgery [10]. In a large prospective study involving more than 1,000 TJA recipients, we showed that poorer pre-operative mental health scores were associated with weight gain after surgery [11]. Obesity is over-represented in TJA candidates (hip patients > 40% obese, knee > 60%) and only 10% show clinically significant weight loss after surgery [11,12]; obesity itself is strongly associated with depression [13]. Pre-operative psychological distress is also associated with excessive analgesic intake, higher rates of hospital readmission, and long-erm mortality [14].

Despite such findings, there is a dearth of literature examining psychological interventions or programs in surgical patients generally, and, to the best of our knowledge, there are no published intervention studies specifically for TJA. Thus, there is a pressing need to examine whether implementing a mental health enhancement program improves postoperative outcomes in patients undergoing TJA, a question with relevance to other surgical programs and to the health of the aged more generally.

Mindfulness training (MT) is derived mainly from Eastern-based philosophical traditions, with mindfulness-based concepts and therapies widely incorporated into experimental and clinical psychology and psychiatry in the past 30 years [15]. Although there is a spectrum of mindfulness-related concepts, we adopt the definition of Kabat-Zinn, where mindfulness is “*the awareness that emerges through paying attention on purpose, in the present moment, and non-judgmentally to the unfolding of experience moment by moment*” [16] (p. 145). This is the basis of an approach known as “mindfulness-based stress reduction” (which we will here refer to as MT for the sake of brevity), the approach employed in most studies of physical health conditions [15].

Benefits of MT have been demonstrated for psychiatric disorders [15,17] and in stressed healthy cohorts [18], but of most relevance to this proposal is its use in older adults [19] and in patients with physically debilitating conditions such as multiple sclerosis [20], fibromyalgia [21], arthritis [22], and chronic pain [23]. Randomised controlled trials in pain patients show efficacy for psychological distress (in general and for symptoms of depression and anxiety in particular), for health related quality of life, as well as for fatigue, pain, functioning, and somatic complaints. Most studies show low attrition (15%) [24] and sustained improvements (particularly in functioning) at up to 3 years [15]. Most psychological interventions for physically ill subjects have arisen out of psychotherapies for the mentally ill (notably cognitive behaviour therapy). In contrast, MT is useful in distressed patients who do not necessarily meet diagnostic criteria for mental illness [25].

Keeping in mind the absence of previously established psychological interventions in arthroplasty, we propose that MT prior to TJA is likely to be a particularly suitable and effective intervention, leading to better outcomes. The primary aim of this research is to determine if psychological well-being and physical recovery are improved in TJA patients if surgery is preceded by a mental health enhancement program. Two exploratory aims of this study will be: i) to compare the cost effectiveness of this combination versus standard of care; ii) to investigate the influence of mindfulness training on candidate mediators of health outcomes drawn from psychological research on adaptation to illness–notably cognitive distortions, illness beliefs, and coping styles.

## Methods

### Experimental design

A randomised controlled trial of individuals undergoing TJA for end-stage arthritis. Patients in the intervention arm will undergo mindfulness training prior to TJA. Patients in the control arm will undergo TJA only. Outcomes will be compared at 12 months after TJA. The study strategy will be registered, constructed, and presented according to the recommendations of the CONSORT statement [26].

### Participants

Participants on the TJA waiting list at St. Vincent’s Hospital Melbourne (SVHM) who present for pre-operative assessment with moderate to severe psychological distress will be invited to participate in the study. Pre-operative assessment is conducted in the orthopaedic pre-admission clinic at SVHM at which point physical and psychological well-being scores are routinely captured using the Short Form-12 (SF-12) questionnaire [27]. Attendance at the orthopaedic pre-admission clinic is mandatory prior to TJA. Here, patients undergo health assessment and education and provide informed consent to TJA. The team comprises an orthopaedic surgeon, resident medical officer, and nursing and allied health staff. After initial screening, potentially suitable patients will be given a plain English statement detailing the nature of the study and the commitment required. For patients willing to proceed, informed consent for the study will be obtained by the research associate.

### Inclusion

i) On the surgical waiting list for primary TJA for end-stage osteoarthritis at SVHM.

ii) Presents with moderate to severe pre-operative psychological distress (SF-12 MCS < 40). The SF-12 measures physical and psychological well-being and is validated for use in the clinical setting and Australian population. A score of less than 40 on the mental component summary indicates moderate psychological distress [27].

### Exclusion

i) Revision surgery or surgery for neoplastic disease.

ii) Inability to provide informed consent due to mental incompetence (e.g., intellectual disability, dementia; mild cognitive impairment would not be cause for exclusion).

iii) Active drug or alcohol use disorder which in the opinion of the investigators makes the patient unsuitable for participation in the trial.

iv) Limited English language fluency.

v) Evidence at interview or on the Memory Complaints Questionnaire [28] of presumptive cognitive impairment requiring clinical assessment.

### Intervention

The intervention group will undergo MT prior to TJA, with a ‘booster’ session at 3 months post-surgery. The 8-week program will be conducted on-site through the Department of Psychiatry at SVHM by MBSR-qualified investigators and will be repeated every 10 weeks during the recruitment phase. The program consists of: i) a personal interview to establish rapport, undertake a brief psychiatric assessment and arrive at realistic goals; ii) weekly group-based classes in mindfulness practice, 2 ½ hours, 10–20 participants, for 8 weeks plus a 7-hour Saturday session in Week 6. MT is manualized with each class covering specific, predetermined MT exercises and topics. Yoga based exercises are adapted to be performed in either sitting or lying, to accommodate the potential mobility limitations of the study population; iii) home-based assignments to encourage regular practice of learned skills, utilising a workbook and CDs with recorded meditation instructions; iv) a post-intervention evaluation interview of personal experiences, goal attainment, and future maintenance of acquired skills; and v) a ‘booster’ day-long workshop 3 months post-surgery. The rationale for this ‘booster’ session is based on a prior randomised trial in which we found that improvements in pain and physical function after TJA plateau by 6 months. Patients with sub-optimal improvements in pain and physical function at 6 months demonstrated a significant decline in their mental well-being scores at 12 months compared to those who experienced optimal physical function, whose mental well-being scores were maintained [29].

### Standard of care

Patients will undergo surgery and post-operative care as per SVHM’s routine TJA program which has been standardised through the use of clinical pathway protocols and validated in a randomised controlled trial [30]. Post-discharge rehabilitation involves either an in-patient or home-based physiotherapy program which is pre-determined during pre-admission clinic assessment using a validated discharge predictor tool [31]. Both programs are standardised and conducted through SVHM’s in-patient or Hospital In-The-Home service and are followed by referral to a community-based physiotherapy program, based on the locality of the patient’s residence. At a pre-admission clinic, all patients receive an instruction booklet outlining the continuum of care for TJA. All patients are reviewed post-surgery in the same clinic at intervals of 6-weeks, 3-, 6-, and 12-months, and annually thereafter.

### Outcome assessments

#### Data capture

Outcomes will be captured by the research associate. Demographic information collected at baseline will include age, gender, co-morbidities, body mass index, and socioeconomic data. We will also collect ‘time’ on the waiting list. All MT sessions will be audio-taped and a random sample will be selected and assessed for adherence to the principles of MT. Fully-itemised costs of healthcare will be captured via SVHM’s hospital network, including administered medications as well as costs of hospital in-patient and out-patient encounters. While beyond the scope of the initial Discovery Project time frame, the investigators will include a longer term follow-up plan in the ethics application to allow scope for continued data capture in the study group at the annual outpatient review to 10 years.

#### Primary outcome

Will be self-reported pain and physical function measured on the Western Ontario and McMaster Universities (WOMAC) Osteoarthritis Index [32]. The WOMAC consists of 24 items covering three subscales: pain (five items), stiffness (two items), and physical function (17 items). The pain and physical function subscales will be used, each subscale transformed to a score ranging from 0 to 100, with a higher score indicating greater pain and physical function. The WOMAC is a widely-used questionnaire specifically designed to evaluate knee and hip osteoarthritis [33,34].

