### Sample size

The sample size calculation was based on the following parameters: i) alpha value = 0.05, 2-sided; ii) power = 80%; iii) expected rates of the primary outcome 1-year post-TJA. To determine the sample size, we reviewed the data from our SVHM joint registry from 2009 to 2010 [44]. Of 1,180 patients who underwent TJA, 40% showed moderate to severe pre-operative psychological distress according to the pre-operative SF-12 MCS score. The mean difference in functional outcome scores at 12 months post-TJA between individuals with moderate to severe pre-operative psychological distress and individuals with no or mild psychological distress was 10 (+20) points. Based on these data, the sample size required in each of the 2 groups is 64. To allow for 15% attrition, 150 patients will be recruited in total. These numbers will also give more than 80% power to detect the expected minimum clinically important difference in pain and functional outcome scores between the combined MT + TJA group and the TJA alone group.

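### WOMAC pain and physical function are both primary with no success rule, but the trial is sized for one functional score, and the power claim for the MCID in both has no stated inputs

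*Protocol article*

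**What the plan says.** - **Outcome.** Under Primary outcome: "Will be self-reported pain and physical function measured on the Western Ontario and McMaster Universities (WOMAC) Osteoarthritis Index". The same paragraph adds: "The pain and physical function subscales will be used, each subscale transformed to a score ranging from 0 to 100". There are therefore two scores. No composite, order or success rule is given.
- **Timing.** The abstract (Methods/Design) says "Primary outcomes will be evaluated by a blinded examiner at baseline, 3 and 12 months post-surgery". Experimental design says "Outcomes will be compared at 12 months after TJA". Sample size refers to "expected rates of the primary outcome 1-year post-TJA".
- **Sample size.** The section gives one error rate, "alpha value = 0.05, 2-sided", 80% power, and one registry contrast in functional scores at 12 months: a difference of 10 with a spread of 20. From these it derives 64 per group, and 150 in total after 15% attrition.
- **Power claim.** The section ends: "These numbers will also give more than 80% power to detect the expected minimum clinically important difference in pain and functional outcome scores". It states no MCID, and no SD for pain.
- **Aim.** The Background gives the primary aim as to "determine if psychological well-being and physical recovery are improved in TJA patients", while psychological well-being is listed under Secondary outcomes.

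**The concern.** A trial with two primary variables needs a rule for what counts as success, and its sample size has to match that rule. Here the sample size matches a trial with one primary variable. If the rule is settled late, the subscale that happens to succeed could be presented as the trial's result. If it is settled later in a strict form (split alpha, or both required), the power has already been fixed by recruiting 150 and will be below the stated 80%.

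The closing power sentence hides this, because it assures the reader that pain is covered too without any figure from which that could be checked.

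**Working it through.** **Inputs (Sample size section).** Difference δ = 10; SD σ = 20 (reading the printed 10 (+20) as mean difference and SD); two-sided α = 0.05; power 80%; 15% attrition; equal groups. So d = 10/20 = 0.5.

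**1. The plan's own figure.** Normal approximation: n = 2(1.960 + 0.842)²(20/10)² = 62.8, so 63 per group. The t-test solution is 63.8, so 64, as stated. Attrition: 128/0.85 = 150.6, against the stated 150. Conversely, 150 × 0.85 = 127.5, about 64 per group. The figure reproduces, for one outcome at 0.05. The exact t-test power at 64 per group is 80.1%, so there is no spare power after the planned attrition.

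**2. Either subscale suffices, each at 0.05.** Familywise error = 1 − P(|Z₁| < 1.96 and |Z₂| < 1.96), with correlation ρ between the two test statistics. The documents give no ρ, so it is assumed:

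| ρ | Familywise error |
|---|---|
| 0 | 1 − 0.95² = 9.75% |
| 0.5 | 9.1% |
| 0.7 | 8.4% |
| 0.8 | 7.8% |
| 0.9 | 7.0% |

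**3. Alpha split equally (0.025 each).** At 64 per group and d = 0.5, power per outcome is 71.2% (t-test). Restoring 80% takes 77.3, so 78 per group; 156/0.85 = 183.5, about 184 recruited instead of 150.

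**4. Both must succeed, each at 0.05.** Familywise error stays within 5%. Joint power, assuming d = 0.5 for pain as well (the documents give no pain effect) and 80.1% marginal power:

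| ρ | Joint power |
|---|---|
| 0 | 0.801² = 64% |
| 0.7 | 71% |
| 0.8 | 73% |
| 0.9 | 75% |

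A simulation of actual t-tests with 64 per group agreed (64% at ρ = 0, 75% at ρ = 0.9).

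**5. The MCID sentence.** With 64 per group, the smallest difference detectable with 80% power is 0.499 × SD.

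- At SD 20 that is 9.98 points. Power is 80.1% at 10 points, 71% at 9, 61% at 8 and 29% at 5.
- For pain, over an assumed SD of 15 to 25, the threshold runs from 7.5 to 12.5 points.
- If nobody dropped out (75 per group), power at 10 points would be 86%, but the plan itself allows for 15% attrition.

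Whether the sentence is true therefore depends on two quantities that the section does not give.

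**The case against.** Several stronger readings are tempting, and the documents do not support them.

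- **That each subscale is tested at 5%, so type I error is inflated.** The article never gives a per-test level; 0.05 appears only as a sample-size parameter. Inflation follows only if either subscale alone counts as success. If both must succeed, the cost is power.
- **That there are four primary tests (two subscales at two times).** The abstract's list of times includes baseline, which cannot be an efficacy endpoint, so it reads as an assessment schedule and agrees with Table 1. Experimental design and Sample size both place the comparison at 12 months. An error rate for four tests is therefore not established. The abstract wording only needs to be brought into line.
- **That the MCID claim is false.** Without an MCID it is unsupported, not refuted. An MCID of 10 points or more at SD 20 would bear it out for function.
- **That well-being is a third primary outcome.** The aim mentions it, but the abstract and the outcome list both make it secondary. This is a matter of aligning the wording and adds no primary test.

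It can also be said that a multiplicity rule commonly sits in the analysis plan, which is not shown, and that this is a condensed article. That is fair, and the missing rule alone would be no finding. What remains is what the article does state: two primary scores, and a sample size built for one. A later plan that split alpha or required both could not recover the power. A later fixed sequence starting with function could, and that is the repair proposed below.

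Finally, the Sample size section speaks only of functional scores and does not name the instrument. Treating them as WOMAC physical function is a reasonable inference, not a stated fact.

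**Conclusion.** The point stands in this form: two primary variables are sized as one, and the power claim for the MCID lacks its inputs. The 64 per group and 150 in total are arithmetically sound for a single functional outcome at 12 months.

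With two co-equal primaries at that size, the plan cannot keep both 5% error and 80% power under any of the three usual rules:

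- **Either suffices:** familywise error about 8%, at most 9.75%.
- **Split alpha:** 71% power per outcome.
- **Both required:** about 64% to 75% joint power.

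A single primary, or a fixed sequence starting with function, keeps both at the present size. These sizes rest on assumed correlations (0.7 to 0.8 for the 8%; 0 to 0.9 for the joint power), on d = 0.5 applying to pain as well as function, and on reading the 20 as an SD.

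**What to change.** 1. Name WOMAC physical function at 12 months as the primary outcome, which matches the basis of the 64 per group. Confirm that the registry functional score is this subscale.
2. Test WOMAC pain at 12 months next, in fixed sequence at two-sided 5%, only if function succeeds.
3. State that the 3-month scores are secondary, so that the abstract agrees with Experimental design. Align the wording of the aim on psychological well-being with its place among the secondary outcomes.
4. Replace the closing power sentence with 80% power for a 10-point difference in function (SD 20), or give the MCID and the SD for each subscale that support the present claim.

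The cost is a change of wording in the protocol and registry entry, with no extra patients. The article reports the trial as open to recruitment, so this can be settled before outcome data are analysed. The downside is that pain can be claimed only if function succeeds. If the investigators prefer co-equal primaries, they should state the rule and size for it: with an equal split and d = 0.5 for both, that is 78 per group, about 184 recruited.

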#### Secondary outcomes

● Psychological well-being: will be derived from the 12-item Short Form Health Survey mental component score [27].

● Quality of Life: will be measured using the WHOQOL-BREF, a 26-item quality of life (QoL) Assessment [35].

● Depression and anxiety: data will be derived from the Hospital Anxiety and Depression Scale (HADS), a validated instrument for detecting states of depression and anxiety and severity of emotional disorder in patients under treatment in hospital medical, surgical, and outpatient departments [36].

● Self-efficacy: will be measured using the Arthritis Self-Efficacy Scale, a 20-item questionnaire [37].

● Mindfulness: the Mindful Awareness Attention Scale (MAAS) is a 15-item measure assessing mindfulness and its role in psychological well-being [38].

● Carver brief COPE questionnaire: a 28-item questionnaire to measure coping styles [39].

● Brief illness perceptions questionnaire: a 9-item measure of illness perceptions [40].

● Irrational scale: a 20-item measure of cognitive distortions [41].

● Health services utilisation: information regarding utilisation of health services, including medications and in- and outpatient services, will be captured by linkage of our database to administrative and clinical databases maintained by SVHM. The latter capture extensive information on all healthcare encounters (in-patient and out-patient) occurring at SVHM’s hospital network, including administered medications as well as fully-itemised costs of healthcare encounters.

